### Patient screening

Participants in the COMBAT trial will be enrollees of the existing STOP smoking cessation program and will therefore be cigarette smokers wishing to quit, or those who have already begun their quit attempt.

Upon enrollment in the STOP program, participants will complete a baseline enrollment survey about their tobacco use and related measures. Alcohol consumption will be measured on the baseline survey using a seven-day timeline followback (TLFB) questionnaire [37] and the Alcohol Use Disorders Identification Test (AUDIT) [38]. Women consuming seven or more and men consuming fourteen or more alcoholic beverages (13.6 g per standard drink) in the past week—as measured by the TLFB—as well as any individual endorsing any episode of consuming five or more drinks on one occasion (AUDIT item 3) will be considered to be exceeding the Canadian Cancer Society (CCS)’s cancer prevention alcohol consumption guidelines [39]. In order for a participant to be eligible for the COMBAT trial, their baseline enrollment survey must be administered by a practitioner, in English, into the online portal in real time, so that the clinical interaction can be supported by the CDSS. Therefore, those patients who are administered the baseline survey on paper, or in French, cannot be included in the trial.

Patient consent for participation in the STOP smoking cessation program will be obtained at the time of enrollment. Individuals younger than 18 years old will enroll with the consent of their legal guardian if required to do so.

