## Methods/design

### Participants

Primary health care clinics in Ontario, Canada, implementing an existing smoking cessation program—the STOP program—at the time of the study are eligible to participate. The vast majority of three types of primary health care clinics across Ontario implement the STOP program: 150 out of 184 family health teams (FHTs), 59 out of 67 community health centres (CHCs), and 17 out of 23 nurse practitioner-led clinics (NPLCs). Clinics enroll their patients into the STOP program using a centralized, online portal; the STOP portal is an online data management and collection tool used by all clinics to complete participant enrollment, record smoking status at each visit, monitor treatment, and receive real-time progress reports. This tool allows for processes to be streamlined and for health care practitioners to track their patients’ progress throughout the program. All those FHTs, CHCs and NPLCs operational in the STOP program as of March 14, 2016 (222 clinics), are eligible for randomization, except one known to use paper-based patient enrollment options exclusively (i.e. any clinic not using the online portal). In total, 221 clinics will be randomized into the COMBAT trial.

To build capacity of all practitioners implementing the STOP program, an interactive webinar will be presented on SBIRT implementation using CDSS, as web-based SBIRT training has shown to be effective for and favourable among primary care practitioners [34]. The webinar audience will include the STOP Community of Practice (*n* = 300) of implementers, physicians, and executive directors, who interact through bi-weekly teleconferences to communicate updates, clarify procedures, address barriers or gaps in program delivery, and share experiences with other practitioners.

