### Randomization

Clinics will be the unit of randomization. Two stratification factors will be defined: clinic type with three levels (FHT, CHC, and NPLC) and clinic size with two levels, resulting in six strata. Actual clinic size, measured as number of trial participants enrolled, is not directly observable a priori; therefore, expected clinic size will be estimated based on past STOP enrollment. Independently for each clinic type, the two levels of clinic size will be set such that expected total enrollment in the two levels will be balanced. Within each stratum, clinics will be randomly allocated in a 1:1 allocation ratio to control (group A) or intervention (group B). Treatment allocation (randomization) for each clinic will be determined for all operational clinics en masse. Any clinics that begin implementing the STOP program after the randomization cut-off date (April 11, 2016) will not be eligible for participation in the COMBAT trial. The random assignment of treatment to clinic will be computer generated using the ralloc command of statistical computer software Stata V.13 [36].

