### Blinding

This pragmatic, cluster trial is designed to evaluate an intervention to change practitioners’ behaviour. Blinding of the clinic via its practitioners will therefore not be possible as the practitioner will be aware of the presence or absence of the portal prompting system.

Participating clinics will not be told of their treatment allocation until the trial begins. Investigators are blinded to the randomization arm. Data analysis will be blinded to treatment allocation.

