### Statistical methods and analysis

Descriptive statistics will compare cluster-level and patient-level baseline characteristics between the two treatment groups.

Results will be analyzed using a generalized estimation approach for fitting logistic regression using a population-averaged method with treatment arm and stratification variables (i.e. organization type and cluster size) regarded as fixed effects and clinic (i.e. cluster) as random effects in the model. To account for clustering, an exchangeable correlation matrix and robust standard errors will be specified [45]. The intra-cluster correlation coefficient will be estimated, and if it is found to be negative, an analysis not adjusting for clustering will be used.

The following baseline variables will be treated as potential confounders: gender; age; body mass index; identifying as First Nations, Inuit or Métis; household income; employment status; educational attainment; depression; AUDIT-C score; heaviness of smoking index; marijuana use; opioid use; treatment for mental health problem; drug treatment; and comorbid conditions. To identify the covariates to be included in the statistical models for the primary, secondary and tertiary analyses, we will fit separate models including each covariate one at a time. The final model will include those covariates such that their inclusion changes the estimated treatment effect by at least 10%. Decisions about the inclusion of covariates will not be based on statistical significance (i.e. *p* values).

As the primary and secondary outcomes will be captured by the online portal, complete case analyses will be used (i.e. imputation will not be used for these outcomes). The tertiary outcome will be available only for those patients who complete a 6-month follow-up survey; therefore, missing data is expected. A single imputation of best-case scenario (i.e. not smoking and drinking within guidelines) and a single imputation of worst-case scenario (i.e. smoking and drinking in excess of guidelines) will be conducted. If the best-case and worst-case scenarios imply different conclusions, a multiple imputation approach that accounts for the clustered structure of the data will be employed.

All analyses will follow an intention-to-treat approach in which clusters and participants are analyzed in the intervention arm to which they were originally assigned.

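### Inclusion in the primary analysis is decided after clinic randomisation by practitioners who know their arm, and the intention-to-treat rule does not protect against arm-dependent inclusion

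*Protocol article*

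**What the plan says.** - **Order of events.** Under Randomization, "Treatment allocation (randomization) for each clinic will be determined for all operational clinics en masse". Patients enrol afterwards, and the same section notes: "Actual clinic size, measured as number of trial participants enrolled, is not directly observable a priori".
- **Who knows the arm.** Under Blinding, "the practitioner will be aware of the presence or absence of the portal prompting system".
- **Who counts.** Under Patient screening, "their baseline enrollment survey must be administered by a practitioner, in English, into the online portal in real time". The stated reason is "so that the clinical interaction can be supported by the CDSS". It follows that "those patients who are administered the baseline survey on paper, or in French, cannot be included in the trial".
- **Whether paper is available.** Under Participants, all operational clinics are eligible "except one known to use paper-based patient enrollment options exclusively". Occasional paper use at the other 221 clinics is not ruled out, and the paper exclusion at patient level presupposes it.
- **What differs by arm.** Under Brief intervention and referral to treatment, the group B portal scores the answers, shows a pop-up for patients above the guidelines and prompts the practitioner to act. Group A uses the same screening tools, but practitioners score them by hand and get no prompt.
- **Analysis.** The primary outcome is the offer of an appropriate resource among patients exceeding the guidelines, as recorded by the portal. It is analysed on complete cases. Under Statistical methods and analysis, "All analyses will follow an intention-to-treat approach", explained there as keeping clusters and participants in their assigned arm.
- **Limitations.** The Discussion mentions unblinded practitioners and contamination between clinics, which it expects to make the estimate conservative. It does not mention selection of patients after randomisation.

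**The concern.** The denominator of the primary outcome is formed after randomisation, through a choice of survey route made by someone who knows the arm. The route is not neutral between arms, since in group B it can bring an alert and a request to act, and in group A it cannot. The eligibility condition is also tied to the decision support being usable.

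If practitioners less inclined to counsel use paper or late entry more often in one arm than in the other, the portal patients in the two arms come from different mixes of practitioners. The comparison of offer rates then loses the protection of randomisation. Keeping each included patient in the allocated arm does not restore it, because the selection has already happened.

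**Working it through.** **1. The plan's own figures.** This point disputes none of them. For orientation, the detectable relative risks in the Effect size section do reproduce. With 189 × 23 = 4347 patients, ICC 0.04, CV 1.04, two-sided alpha 0.05 (sidedness assumed) and 80% power:
- L = 23 × 0.04 / (23 × 0.04 + 0.96) = 0.489
- Design effect = (1 + 22 × 0.04) / (1 − 1.04² × L × (1 − L)) = 1.88 / 0.730 = 2.576
- Effective n per arm = (4347 / 2) / 2.576 = 844
- Detectable RR = 1.447 at a control rate of 0.1 and 1.041 at 0.9, against 1.45 and 1.04 stated.

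The benchmark used below is the revised target in the same section, a relative risk of 1.20.

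**2. Effect of selective inclusion when there is no true effect.** Let p be the offer rate among all risky drinkers in both arms. Let d be the share of group B risky drinkers who leave the denominator by route, and let k be their offer rate relative to p. None leave in group A. Then

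observed group B rate = p(1 − kd) / (1 − d), so RR = (1 − kd) / (1 − d).

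The values of d and k are assumptions; the article gives neither.

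| Patients who leave | d = 5% | d = 10% | d = 15% | d needed for RR 1.20 |
|---|---|---|---|---|
| None would have been offered (k = 0) | 1.05 | 1.11 | 1.18 | 1 − 1/1.2 = 16.7% |
| Offered at half the average rate (k = 0.5) | 1.03 | 1.06 | 1.09 | 0.2/0.7 = 29% |
| Offered at the average rate (k = 1) | 1.00 | 1.00 | 1.00 | not reached |

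If the patients who leave are more likely than average to be offered a resource, the bias reverses: k = 1.5 and d = 10% give 0.85/0.90 = 0.94. If both arms have the same d and the same k, the factors cancel and RR = 1.00. Bias therefore needs a difference between arms and a link with offering.

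**3. The upper bound in terms of non-offered patients.** With k = 0, d = e(1 − p), where e is the share of non-offered group B patients who leave. Reaching RR 1.20 needs e = 0.167/(1 − p), which is 19%, 24% and 33% at p = 0.1, 0.3 and 0.5.

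**4. Effect on the test.** Take the revised size of 6158, the observed mean cluster size of 12.71 and CV of 1.38, and assume the ICC is still 0.04.
- Design effect = 1 + ((1.38² + 1) × 12.71 − 1) × 0.04 = 2.437
- Effective n per arm = 3079 / 2.437 = 1264
- At p = 0.3 and k = 0, the chance of a significant result with no true effect rises from 5% to about 23% for e = 10% (observed rate 0.323, RR 1.08).
- For e = 20% it is about 75% (observed rate 0.349, RR 1.16).

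These are upper-bound scenarios, since every patient who leaves is taken as not offered.

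**5. What restoring the patients does.** With k = 0 and d = 10%, adding the missing 10% back as not offered gives p/0.9 × 0.9 = p, so RR returns to 1.00.

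**The case against.** The strongest reply is that nothing shows practitioners avoiding the alert, and that the workflow makes avoidance unlikely to be selective.

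- **Timing of the alert.** It fires only after the portal has scored the answers. When choosing the route, the practitioner does not yet know whether the survey will flag this patient. This stands. Any avoidance would act mainly by practitioner or session and would also move patients who would have been offered a resource. It moves the plausible range away from k = 0 but does not force k = 1.
- **An easier exit.** A group B practitioner may decline inside the portal, and that patient still counts. This stands and weakens the motive to use paper.
- **Direction.** A reader might infer that the rule removes non-offered patients from group B and so favours the intervention. The article does not support this. The rule is the same in both arms, and automatic scoring could equally draw busy, low-offering practitioners to the portal in group B and lower its rate.
- **Misrecording.** A reader might also suspect that drinking would be under-recorded to avoid the prompt. Nothing in the article suggests it.
- **Intention-to-treat.** The article explains the term as analysis by assigned arm. Patients surveyed on paper never become participants, so there is no contradiction. The term simply does not reach this problem.
- **Existing checks.** Baseline characteristics will be compared by arm, and AUDIT-C and other case-mix variables are listed as potential confounders. It would therefore be too strong to say that selection cannot be seen. The check is partial: it describes included patients only and does not measure practitioners' willingness to offer.
- **Left to the analysis plan.** Route counts by arm may well be in a plan that is not shown, and their absence from an article is no fault. The point rests instead on the eligibility rule and the intention-to-treat statement, both of which this article fixes.

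**Conclusion.** The point holds as a structural weakness of unknown direction and size. Inclusion depends on a route chosen after randomisation by practitioners who know their arm, and that route triggers an alert in one arm only. Neither the analysis section nor the limitations deals with arm-dependent inclusion.

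The size rests entirely on assumed d and k, with diversion in group B only and no true effect. Moderate diversion can matter against a target of 1.20, but the whole target is reached only at the extreme (16.7% lost, all non-offered) or with heavier loss (29% at half the average offer rate). With no link between route and offering there is no bias. The article does not show that any bias has occurred. The point is worth acting on because the check is cheap and, with recruitment continuing and investigators reported as blinded, can still be prespecified.

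**What to change.** Keep the portal population as primary, and prespecify two checks.

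(a) A clinic-adjusted comparison by arm of two shares: English STOP enrolments at randomised clinics that are excluded for paper or late entry, and portal enrolments that screen above the guidelines.

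(b) A sensitivity analysis by allocated arm that adds the English enrolees excluded by route. Where their alcohol answers were entered later, add only those exceeding the guidelines, so that the risky-drinker denominator is kept. Otherwise use all English enrolees. The article says that the portal records offers but not whether offers to paper patients are recorded, so bracket unrecorded offers as all offered and as all not offered.

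Report the primary result as open to selection bias if (a) differs by arm or (b) changes the conclusion. State that intention-to-treat applies to clinics and included patients only, and add selection after randomisation to the limitations.

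Cost: a little extra analysis. It relies on programme records of enrolment route, which should exist because the exclusion cannot be applied without them. The estimate in (b) will be diluted or given as a bracket, so it serves as a check and not as a replacement for the primary result. The sample size does not change.

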### Brief intervention and referral to treatment

In clinics assigned to group B (intervention), practitioners will receive an automated decision aid tool (CDSS) embedded in the STOP program’s online portal. The tool will provide decision support as part of the STOP program’s clinical workflow in three steps. In the first step, the tool will automatically score screening tool responses and identify to practitioners, in the form of a pop-up message, those patients who reported consuming alcohol in excess of CCS cancer prevention guidelines. In the second step, the tool will prompt practitioners to provide a brief alcohol reduction or abstinence intervention; the tool will provide guidance on how to conduct a brief intervention, or allow practitioners to conduct an intervention of their own, or to decline to conduct an intervention at that time. In the third step, practitioners will be asked to provide the patient with the appropriate educational, alcohol resource.

The trial will assess the effect of an online portal-based computer decision support system on health care practitioners’ provision of educational resources addressing alcohol consumption (i.e. “Referral to Treatment” portion of SBIRT) to patients who are exceeding cancer prevention alcohol drinking guidelines and engaging in an attempt to quit smoking. We designed two educational resources, one encouraging alcohol reduction, and one encouraging alcohol abstinence. Practitioners will be encouraged to deliver the alcohol reduction resource to patients exceeding CCS cancer prevention alcohol consumption guidelines. The alcohol reduction resource was adapted from four evidence-based resources including the National Institute on Alcohol Abuse and Alcoholism’s “Rethinking your Drinking” [40]; BC Partners for Mental Health and Addictions’ “Problem Substance Use Workbook” [41]; Capital Health Nova Scotia’s “My Choice: A Workbook For Making Changes” [42]; and College of Family Physicians of Canada and Canadian Centre on Substance Abuse’s “Drinking Smart: Your Health and Alcohol Consumption” [43]. In order to ensure the resources reflect the needs and interests of the population of interest, the adaptations were shaped by a community-informed engagement event with clients enrolled in the STOP program who reported drinking alcohol above the Canadian Cancer Society’s low-risk drinking guidelines.

However, participants who exceed cancer prevention alcohol consumption guidelines may be alcohol dependent, in which case, advice to abstain from alcohol consumption is warranted [44]. For participants scoring above a brief screen (AUDIT-C) cut-off (female >2 points; male >3 points), the online portal will launch a mandatory, full AUDIT (AUDIT-10) screen for alcohol dependence risk [38]. Practitioners will be trained to advise participants scoring above the AUDIT-10 cut-off (20 points) to abstain from alcohol consumption and to provide the alcohol abstinence resource including contact information for a provincial referral system (http://www.connexontario.ca/) for further treatment at local addiction programs.

In clinics assigned to group A (control), practitioners will administer the same alcohol screening tools and have access to the same educational resources as group B. However in order to identify patients who report consuming alcohol in excess of CCS cancer prevention guidelines, they will have to score patients’ screening tool responses (as they will not receive prompts from the portal) and decide which educational resource is the most appropriate for their patient.

Refer to Fig. 1 for a visual depiction of the study work flow.

**Fig. 1 Fig1:**
[figure not shown]
Study workflow diagram

All patients will be contacted to complete a six-month follow-up survey, where they will be asked about their current drinking and smoking behaviours.

### Outcomes

The primary outcome of the study, measured at the cluster level, will be the offer of an appropriate educational alcohol resource, reduction or abstention, to patients exceeding the cancer prevention alcohol consumption guidelines upon completion of STOP smoking cessation program enrollment. This dichotomous outcome is recorded by the STOP program’s online portal for each enrolling participant.

Given that patients can refuse practitioners’ offer of resources, the secondary outcome of the study, measured at the cluster level, will be the acceptance of the educational alcohol resource by patients exceeding the cancer prevention alcohol consumption guidelines. This dichotomous outcome is also recorded by the STOP program’s online portal for each enrolling participant.

The tertiary outcome, measured at the patient level, will be patient abstinence from smoking, and alcohol consumption within cancer prevention guidelines, at the 6-month follow-up survey as recorded in the STOP program’s online portal. Smoking abstinence will be defined by a negative response to the seven-day point prevalence question, “Have you had a cigarette, even a puff, in the last 7 days?” Alcohol consumption at follow-up will be measured using the same survey items as those used in the baseline enrollment survey, described previously. Alcohol consumption within CCS guidelines will be defined as the inverse of alcohol consumption in excess of CCS guidelines.

### Effect size

Based on measures of alcohol consumption used in the STOP Program prior to the start of the COMBAT trial, and accounting for intra-cluster correlation within each clinic as well as unequal enrollment by clinic, we assumed an enrollment of 23 participants per clinic over the 12-month course of this trial, in 189 clinics, for a total of 4347 subjects exceeding CCS guidelines, with enrollment size varying by a coefficient of 1.04. We set alpha = 0.05 and power = 80% and estimated an intra-cluster correlation coefficient of 0.04. Since there were no available estimates of the trial’s primary outcome measure prior to the initiation of the trial, the minimum detectable effect size was estimated for a range of values of *P*
_1_, the proportion of control group enrollments in which practitioners delivered the brief intervention. The estimated detectable effect size ranged from a relative risk of 1.45 (if *P*
_1_ = 0.1) to 1.04 if (*P*
_1_ = 0.9).

An interim analysis in the form of a power calculation was conducted at the 8-month mark once estimates of *P*1 (defined above) were available. As described above, we used a method that accounts for intra-cluster correlation within each clinic as well as unequal enrollment by clinic, now incorporating the updated measures of alcohol consumption introduced with the start of the trial. The observed average cluster size was 12.71 and cluster sizes varied by a coefficient of 1.38. Setting alpha = 0.05, the analyst, unblinded to treatment allocation, obtained an estimate of *P*
_1_ from the data collected to that date. To detect a relative risk of 1.20, the required sample size was estimated to be 6158. Therefore, the recruitment period will be extended until such a time as that sample size is achieved.

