## Discussion

This novel web-based platform for prevention interventions could shift the current practice of addressing alcohol and tobacco separately in the same patient to one where it is feasible for practitioners to provide a combined intervention for both behaviours using an evidence-informed computer-guided intervention. This program may also overcome the barrier of low implementation rates of brief interventions for alcohol use in primary care by automating best practices for cancer prevention.

By the end of this study, we will have intervened with 221 primary care clinics, which in turn will have the opportunity to intervene with approximately 4800 smokers who drink above CCS guidelines.

An important strength of this protocol is the use of a cluster randomized trial design to test a clinically important question for primary care sites in Ontario. In the field of implementation science, this study examines an innovative, web-based strategy to facilitate the uptake of evidence-based intervention practices in a primary care setting. The approach is pragmatic (as defined by PRECIS-2) [47], highly valuing external validity. Future studies will be able to use knowledge gained from this study to model computer-facilitated, just-in-time decision support strategies for other types of clinical encounters especially those requiring behaviour change such as nutrition and weight loss, or management of diabetes or hypertension.

The use of a web-based portal overcomes issues related to incompatibility across various electronic medical records in primary care settings. The permanent addition of an alcohol intervention to the STOP web-based portal would lead to a system-wide implementation of integrated alcohol and tobacco care pathways at relatively low cost. Therefore, scaling up is possible at low cost due to high adoption of the platform. In the field of health systems research, findings from this study can inform future planning and integration of other behavioural interventions—such as physical activity and mood management—into primary care settings. This program can also be scaled out beyond primary care to Addiction Agencies and Public Health Units.

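### The re-estimated target of 6158 appears to use the month-8 cluster size of 12.71, but in a closed set of 221 clinics the mean size must more than double, so power for a relative risk of 1.20 is below 80%

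*Protocol article*

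**What the plan says.** All the sample-size figures are in the Effect size section of the protocol article.

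- **Initial calculation.** It assumes 23 patients per clinic over 12 months in 189 clinics, 4347 in total, with a coefficient of variation (CV) of cluster size of 1.04. The error rates and ICC are given as "We set alpha = 0.05 and power = 80% and estimated an intra-cluster correlation coefficient of 0.04". The detectable relative risk is 1.45 if the control proportion P1 is 0.1, and 1.04 if P1 is 0.9.
- **Month-8 re-estimation.** It is said to follow the same approach. The cluster data are "The observed average cluster size was 12.71 and cluster sizes varied by a coefficient of 1.38", and the result is "To detect a relative risk of 1.20, the required sample size was estimated to be 6158". Recruitment then continues until that number is reached. The P1 obtained, the ICC and the power are not given for this step.
- **Clinics.** Participants: "In total, 221 clinics will be randomized into the COMBAT trial". Randomization rules out new ones: "Any clinics that begin implementing the STOP program after the randomization cut-off date" are not eligible.
- **Discussion.** It still speaks of "the opportunity to intervene with approximately 4800 smokers who drink above CCS guidelines".

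**The concern.** In a cluster trial the required number of patients depends on how many come from each cluster. If recruitment grows by adding clinics, the mean cluster size can stay where it is. If it grows by recruiting longer in the same clinics, the mean size rises, the design effect rises with it, and each further patient adds less information.

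This trial can grow only in the second way. The initial calculation respected this by using the size expected over the full recruitment period. For the re-estimation the only size reported is the one observed part-way through. If that size was used, 6158 is too small for its stated purpose.

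What is at stake is the recruitment target for the primary outcome. A null primary result at 6158 would be read as adequately powered evidence against a relative risk of 1.20, when the power could be nearer 60%. Type I error and the validity of the planned clustered analysis are not affected.

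**Working it through.** **Inputs from the protocol article.** Alpha 0.05; month-8 mean size 12.71 and CV 1.38; target relative risk 1.20; N = 6158; 221 clinics (189 in the initial calculation); planned CV 1.04; 1:1 allocation.

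**Assumptions.** Two-sided alpha; ICC 0.04 and 80% power carried forward to month 8; 6158 counts patients above the drinking guidelines, as 4347 did. P1 is back-solved.

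**Cluster size.** 6158/12.71 = 484.5, so about 485 clinics would be needed at the reported size. With 221 clinics the mean at 6158 is 6158/221 = 27.9, which is 2.19 times 12.71. With 189 clinics it is 6158/189 = 32.6.

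**Formulas.** With mean size m and L = m·ICC/(m·ICC + 1 − ICC), the relative-efficiency design effect is DE = (1 + (m − 1)·ICC) / (1 − CV²·L·(1 − L)). It suits an exchangeable working correlation. The simpler alternative is DE = 1 + ((1 + CV²)·m − 1)·ICC. Either one multiplies the usual two-proportion sample size.

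**Reproducing the initial figures.** 23 × 189 = 4347. For m = 23, CV = 1.04 and ICC = 0.04, L = 0.92/1.88 = 0.489, and DE = 1.88/(1 − 1.0816 × 0.2499) = 2.58. The detectable relative risks are 1.447 at P1 = 0.1 and 1.041 at P1 = 0.9, against the stated 1.45 and 1.04. The simpler formula gives 1.474 and 1.043. The relative-efficiency form is therefore the closer match and is used for the main figures.

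**Month 8.** For m = 12.71 and CV = 1.38, L = 0.5084/1.4684 = 0.346, and DE = 1.4684/(1 − 1.9044 × 0.2264) = 2.58. Effective N is 6158/2.58, about 2386. This gives 80% power for a relative risk of 1.20 if P1 is about 0.26. Because P1 is not reported, 6158 itself cannot be confirmed.

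**At 6158 in 221 clinics.** For m = 27.9 and CV = 1.38, L = 1.1146/2.0746 = 0.537, and DE = 2.0746/(1 − 1.9044 × 0.2486) = 3.94. Effective N is about 1563.

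**Power.** To a close approximation, power = Φ(2.80·√(DE at 12.71 / DE at final size) − 1.96), which hardly depends on P1. For 2.58/3.94 the square root is 0.809, and power = Φ(0.31), about 62%.

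| Clinics | Final CV | DE | Power for RR 1.20 | RR detectable at 80% |
|---|---|---|---|---|
| 221 | 1.38 | 3.94 | 62% | 1.25 |
| 221 | 1.04 | 2.84 | 76% | 1.21 |
| 189 | 1.38 | 4.23 | 59% | 1.26 |
| 189 | 1.04 | 3.08 | 73% | 1.22 |

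**Sensitivity.** The grid covers ICC 0.01 to 0.10 (the same value at month 8 and at the end), final CV 1.04 or 1.38, 189 or 221 clinics, and both formulas. Power runs from about 46% (simpler formula, ICC 0.10, 189 clinics, CV 1.38) to about 77% (relative-efficiency form, ICC 0.06, 221 clinics, CV 1.04). It never reaches 80%. At ICC 0.04 with 221 clinics, the shortfall disappears only if the final CV falls to about 0.89 (relative-efficiency form) or 0.57 (simpler formula). Both are below the planned 1.04.

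**The case against.** The strongest reply is that the premise is inferred. The article calls 12.71 an observed value and never says that it was the size entered. It describes the method as the one used before, and that calculation took a full-period size. If the analyst projected the final size, 6158 fits a relative risk of 1.20 at 80% power with P1 of about 0.34 (relative-efficiency form) or 0.36 (simpler formula), at ICC 0.04, CV 1.38 and 221 clinics. There would then be no shortfall. This stands as a limit on certainty. It does not remove the point, because no projected size is reported and the figures as printed do not fit a closed set of 221 clinics.

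A second reply is that the CV may also change by the end of recruitment. This stands too: a return to 1.04 brings power to about 76%, a loss of only a few points. That is why both CV values are shown.

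Two stronger inferences should not be drawn:

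- **That no extension could ever reach 80% power.** Under the simpler formula at ICC 0.04, CV 1.38 and 221 clinics, effective N is capped at 221/(0.04 × 2.90), about 1,900, against about 2,527 needed. That formula fits the protocol's own figures less well. Under the relative-efficiency form the target is reached at about 13,000 patients (CV 1.38) or 7,500 (CV 1.04).
- **That power collapses because the true ICC is 0.10 while 6158 was built on 0.04.** Nothing in the article points to an ICC of 0.10. That the article reports no updated ICC does not show that none was estimated, since a condensed article may leave this to a fuller document.

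**Conclusion.** The point holds on the plain reading of the Effect size section. The reported month-8 cluster size, the target of 6158 and the closed set of 221 clinics do not fit together, and a design effect taken at 12.71 understates the need. In the case closest to the protocol's own method (ICC 0.04, 80% planned power, 221 clinics), power for a relative risk of 1.20 is about 62% with CV 1.38 and about 76% with CV 1.04. The corresponding detectable relative risks are about 1.25 and 1.21. Over the wider range examined, power is about 46% to 77%.

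The direction is firm if 12.71 was used. The size depends on an ICC, a P1, a planned power and a final CV that the article does not report for this step. If a projected size was used, the defect is only that the wrong cluster size is printed. The figure of about 4800 in the Discussion agrees with neither 4347 nor 6158. That is a separate, minor inconsistency and has no bearing on power.

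**What to change.** Redo the month-8 calculation with the following inputs:

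- the number of clinics fixed at those actually enrolling (221 or fewer);
- the mean cluster size projected to the end of recruitment, 6158 divided by that number;
- the CV projected to the same point;
- the ICC estimated from the month-8 data.

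State these inputs with P1 and the planned power. Replace the claim that 6158 is what a relative risk of 1.20 requires with the power at 6158, or the relative risk detectable there with 80% power. If a projected final size was in fact used, report it in place of 12.71. Bring the Discussion's figure of about 4800 into line with the current target.

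The cost is one re-run calculation and revised wording. If 12.71 was used, the stated power or detectable effect becomes less favourable. No additional patients and no change to the design or analysis are asked for.
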